### MasterChef: Nursing Edition

This monthly workshop is innovative in combining gamified learning, cooking self-efficacy, mindful eating, and nutrition education for prelicensed nursing students. The course outline consists of (1) mindful eating concepts, (2) nutrition education, (3) participants designing their own healthful and accessible recipe, (4) participants mindfully eating and voting on their favorite meal, and (5) discussion and application to clinical practice. Participants are also encouraged to do 2 “homework” assignments per week, each emphasizing healthy eating or mindfulness behaviors. Participants also receive ingredients for recreating their healthful recipe at home and a “dorm-friendly” recipe book developed by a registered dietitian nutritionist. All students, staff, and faculty are encouraged to join, but students in designated courses receive credit for attendance.

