### MasterChef Analysis

MasterChef will be evaluated initially for feasibility through a qualitative focus group design along with an expert content analysis. After modifications to the program based on feasibility analysis, the intervention will be evaluated using a matched-based cohort design with the non-MasterChef control group selected based on gender, ethnicity, and year in college matched-based design, with a focus on gender, ethnicity, and year in college. Descriptive and frequency statistics were used to analyze the sample’s baseline and demographic data. A 2-way repeated-measures analysis will be used to assess significant changes in baseline and postintervention outcomes within the experimental group and as a comparison with the control. Participants will complete the aforementioned nutrition measures before the week-long Fall 2023 program delivery, directly after the program, and again at the end of the semester. A control will be recruited through a matched-based design. A 2-way repeated-measures ANOVA will be used to identify significant changes between baseline data, postintervention data, and follow-up data between the intervention and control group. The program will also be implemented in the format of monthly workshops. A multivariate ANOVA will be used to compare health outcomes between curriculum formats. Multiple linear regressions will be used to identify predictors of diet quality using the combined fall and spring samples. Significance levels will be set at *P*<.05.

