#### Nutrition

Nursing students report poor diet quality and dietary behaviors elicited by high levels of perceived stress, peer influence, and academic workload [62]. The impact of mindful eating may mediate this relationship [63]. Mindful eating describes applying mindfulness practices to internal hunger and satiety cues and incorporating a nonjudgmental, self-compassion–led viewpoint in navigating dietary choices [64]. Mindful eating interventions effectively improve several health behaviors, including reducing extreme dieting behaviors, improving portion control, and weight reduction within some populations [65,66]. This study aims to examine the effect of the newly developed program, MasterChef Nursing Edition, on nursing students’ diet quality, resilience, burnout, and well-being.

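### The MasterChef week-long versus monthly comparison is a MANOVA between non-randomised formats with no baseline, control or semester term stated, so baseline or semester differences could be mistaken for a format effect

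*Protocol article*

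**What the plan says.** All references are to the Protocol article.

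- **Format comparison (MasterChef Analysis).** "A multivariate ANOVA will be used to compare health outcomes between curriculum formats". The sentence gives no covariate, control group, semester or assessment time.
- **Timing of the week-long format (same section).** The nutrition measures are taken "before the week-long Fall 2023 program delivery, directly after the program, and again at the end of the semester".
- **Timing of the monthly format.** "The program will also be implemented in the format of monthly workshops", with no semester given. The section MasterChef: Nursing Edition describes the program in general as monthly ("This monthly workshop is innovative in combining gamified learning"), again without a semester.
- **Hint of a link between format and semester.** The next analysis, a regression, looks for "predictors of diet quality using the combined fall and spring samples". The only dated fall delivery is the week-long one.
- **Effectiveness analysis (same section).** A 2-way repeated-measures ANOVA looks for "significant changes between baseline data, postintervention data, and follow-up data between the intervention and control group". Controls are matched on gender, ethnicity and year in college. Semester is not among the matching factors.
- **Baselines (Nutrition Assessments).** Participants must complete the nutrition assessments before attending a workshop.
- **Outcomes in the aim (Comparisons With Prior Work, Nutrition).** Four are named: diet quality, resilience, burnout and well-being. The three MasterChef assessments are described as nutrition measures only.

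**The concern.** Students are not allocated to a format at random, so the two groups may differ before either program starts. If the monthly workshops run mainly in spring, format and semester also move together. A MANOVA of outcomes by format, taken as written, cannot separate these differences from the effect of the format.

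The article shows the needed protections elsewhere. The MasterChef effectiveness analysis uses baseline data and matched controls, and the MBSR Analysis section compares post-intervention levels while controlling for pre-intervention levels. Neither protection is stated for the format comparison, although the baseline scores would already be in hand.

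At stake is the credibility of any statement that one curriculum format works better than the other. A smaller issue sits beside this: the aim names resilience and burnout, but the MasterChef analysis does not say where those scores come from.

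**Working it through.** **What can be reproduced.** Nothing. The article gives no sample size, effect size, SD or power for this comparison. What follows illustrates how sensitive the stated test is.

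**Inputs.**
- From the article: significance level 0.05 (MasterChef Analysis); two formats.
- Assumed: n = 20, 30 or 50 per format; p = 4 outcomes; common correlation r = 0.3; no true format effect; a shift of d SD on every outcome between the two groups, fully aligned with format.

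**Step 1: the MANOVA as written.** With two groups the test is Hotelling's T². It rejects with the probability given by a noncentral F on p and 2n − p − 1 degrees of freedom. With equal shifts and equal correlations the noncentrality is

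λ = (n/2) × p·d² / [1 + (p − 1)r].

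For d = 0.3: p·d² = 4 × 0.09 = 0.36; 1 + 3 × 0.3 = 1.9; 0.36/1.9 = 0.1895.
- n = 20: λ = 10 × 0.1895 = 1.89, on 4 and 35 df
- n = 30: λ = 15 × 0.1895 = 2.84, on 4 and 55 df
- n = 50: λ = 25 × 0.1895 = 4.74, on 4 and 95 df

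Probability of a significant result with no format effect:

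| Assumed shift | n = 20 | n = 30 | n = 50 |
|---|---|---|---|
| 0 SD | 5% | 5% | 5% |
| 0.2 SD | 9% | 12% | 17% |
| 0.3 SD | 15% | 22% | 36% |
| 0.5 SD | 37% | 56% | 82% |

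**Step 2: what adjustment achieves.** This is a one-outcome simulation: 4,000 runs, 30 per cell, assumed baseline-to-post correlation 0.5, no format effect. Three analyses are compared: post score only; post score adjusted for baseline; and baseline adjustment plus same-semester controls, where the format contrast is the format-by-group interaction.

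| Assumed semester difference | Post only | Baseline-adjusted | Baseline + same-semester controls |
|---|---|---|---|
| None | 5% | 5% | 5% |
| 0.3 SD at baseline and post | 20% | 9% | 5% |
| 0.5 SD at baseline and post | 48% | 19% | 5% |
| 0.3 SD arising after baseline | 22% | 26% | 4% |
| 0.5 SD arising after baseline | 48% | 59% | 5% |

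Baseline adjustment reduces the error when the groups already differ at the start. It does not help when the semester difference develops after baseline. In that case it raises the rate, because the residual variance falls while the bias stays. Only same-semester controls bring the rate back to about 5%. The simulation has no self-selection into format that acts beyond the baseline score, so it says nothing about that source of bias.

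**Step 3: resilience and burnout.** The Nutrition Assessments subsections cover mindful eating, food preparation, body appreciation, weight satisfaction and diet quality. The Oldenburg Burnout Inventory and Brief Resilience Scale are in the Comprehensive Wellness Survey, given in weeks 4 and 14 of each fall and spring semester and tracked by ID code. The data exist; the link to the MasterChef analysis is not stated.

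**The case against.** The strongest reply is that this is a condensed article whose analysis plan is not shown, and that silence about covariates is not a decision to leave them out. Baselines and matched controls are planned for MasterChef, and the MANOVA could be run on change scores. This is right as far as it goes: a reader might infer that the plan rejects baseline adjustment, and the article does not say so. What remains is that the article names a specific test for a specific non-randomised contrast and states its protections only for the neighbouring contrasts.

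Several stronger readings are tempting and are not supported:

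- **Format is tied to semester.** No semester is given for the monthly workshops, and the program is called monthly in general, so a fall monthly series is not excluded. The pooled fall and spring samples belong to a regression of diet quality, not to a schedule of formats.
- **A semester effect will be read as a format effect.** Bias needs a real difference. The article describes stress rising within each semester and gives no fall-to-spring difference.
- **The choice of format depends on this test.** The Discussion ties curriculum adoption to demonstrated effectiveness, which the matched-control analysis addresses.
- **Resilience and burnout go unmeasured.** The wellness survey already collects them.
- **The repeated-measures ANOVA will discard incomplete participants.** No rule on missing data is stated, so no loss can be claimed.

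**Conclusion.** The point holds in limited form. The format comparison is planned as a MANOVA between non-randomised groups without a stated baseline, control or semester term, and the baseline data needed for a better analysis are already collected. Differences in starting level or semester could be mistaken for a format effect.

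The size is not known from the article. Under an assumed 0.3 SD shift, four outcomes correlated 0.3 and 20 to 50 per format, the false-positive rate would be about 15% to 36%. It is 5% if there is no shift. These figures also assume complete alignment of the shift with format, which is an inference if the source is semester. They are illustrations and do not predict this study's error rate.

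The outcome point is smaller: resilience and burnout are measured elsewhere in the study and need only be linked to the MasterChef analysis.

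**What to change.** 1. State in which semester or semesters each format runs, and when the monthly participants are assessed after baseline. The three assessment times are given only for the week-long delivery.
2. Compare formats on the post-program and end-of-semester outcomes adjusted for the pre-program score. ANCOVA or MANCOVA would serve, or a mixed model of the follow-up scores with time in the model. In a mixed model, baseline should enter as a covariate only and not also as a response.
3. Where matched controls from the same semester are available for each format, estimate each format's effect against its own-semester controls and take the difference between the two effects as the format contrast. Where they are not available, label the comparison exploratory and confounded with semester.
4. For resilience and burnout, use the week-4 and week-14 survey scores linked by ID in the MasterChef-versus-control analysis, after checking that week 4 precedes the program.

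**Cost.** Steps 1, 2 and 4 change wording and use data already planned. Step 3 needs controls for the monthly format from the same semester. It is also less precise: with n in each of four cells, the variance of the contrast is 4σ²/n instead of 2σ²/n, so its standard error grows by √2, about 1.41. Self-selection into a format remains under every option and should be stated as a limitation.

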## Discussion

### Principal Findings

Stress and burnout among nurses and students is not a new phenomenon. However, the COVID-19 pandemic has exacerbated the challenge and demonstrated the urgency in mitigating stress to improve well-being and resilience and reduce burnout. As the United States faces a looming nursing shortage and burnout crisis, more research that includes large sample sizes and longitudinal studies is needed to determine and implement resilience-building and stress reduction interventions within nursing programs [12]. Interventions that demonstrate effectiveness at improving student retention, reducing the risk of burnout, and improving resilience and well-being will be infused into a course, which will be embedded as part of the standard nursing curriculum.

### Comparisons With Prior Work

#### WellNurse Room

Effective strategies to promote resilience and reduce burnout require system and environmental interventions [43]. The room contains floral murals, live plants, aromatherapy, meditation cushions, light therapy, coloring books, and tactile engagement. The WellNurse room is stocked with meditation cushions and a massage therapy table. Weekly mindfulness sessions are offered to support MBSR practices. A licensed massage therapist provides complimentary massage therapy in 15- to 30-minute sessions. Aromatherapy and massage therapy have shown stress-reducing effects [44,45]. This study aims to understand how environmental changes may influence nursing students’ resilience, stress, and well-being.

#### Mindfulness-Based Stress Reduction

Extensive literature supports MBSR as an effective intervention in reducing burnout among nurses [46-52].

MBSR, meditation, and mindful movement are further effective in treating posttraumatic stress disorder and depression symptoms [35], preventing substance use relapse, and curbing binge-eating behavior [53-55]. MBSR has demonstrated better outcomes for binge-eating than cognitive-behavioral therapy [56] and is as effective as anxiolytic medication in managing anxiety disorders [57].

College students with mindfulness training have been able to better resist the negative impact of stress during challenges [58], and mindful movement and meditation are both recommended as nonpharmacologic interventions to reduce stress and anxiety among college students [43]. Among medical students, these practices were found to improve happiness, self-confidence, endurance, and patience [59]. Systematic reviews have demonstrated that MBSR decreases stress and burnout and increases resilience, coping, and job satisfaction among nurses [60,61]. Given MBSR’s significant benefits with regard to physical and mental health and its demonstrated impact in nursing and college student populations, this evidence-based intervention was an ideal fit for the WellNurse nursing students. This study aims to examine the effect of MBSR on graduate and undergraduate nursing students’, faculty’s, and staff’s resilience, perceived stress, mindfulness, and burnout.

#### Nutrition

Nursing students report poor diet quality and dietary behaviors elicited by high levels of perceived stress, peer influence, and academic workload [62]. The impact of mindful eating may mediate this relationship [63]. Mindful eating describes applying mindfulness practices to internal hunger and satiety cues and incorporating a nonjudgmental, self-compassion–led viewpoint in navigating dietary choices [64]. Mindful eating interventions effectively improve several health behaviors, including reducing extreme dieting behaviors, improving portion control, and weight reduction within some populations [65,66]. This study aims to examine the effect of the newly developed program, MasterChef Nursing Edition, on nursing students’ diet quality, resilience, burnout, and well-being.

#### Fitness

Physical activity reduces stress and anxiety [67-70], and stress and anxiety are associated with increased burnout and decreased resilience among nurses [52]. A review of 37 studies on Fitbit-based interventions demonstrated the effectiveness of this wearable technology for physical fitness support; wearing a Fitbit significantly increased daily step counts and moderate to vigorous physical activity and significantly decreased weight [69]. Although students have access to healthy food and physical fitness environments, nursing programs do not systematically integrate support systems that promote physical well-being [12,71-74]. The aim of this study is to examine the effect of fitness interventions on nursing students’, faculty’s, and staff’s burnout, resilience, fitness, and well-being.

### Conclusions

WellNurse aims to examine multiple resilience-building and stress-reducing strategies while creating a culture that promotes student, faculty, and staff well-being in concert with academic and clinical preparedness and job satisfaction. Dissemination of findings will be released as they are available with an anticipated release date of initial findings in 2024.

## Abbreviations

DEI: diversity, equity, and inclusion
MBSR: Mindfulness-Based Stress Reduction
PSS: Perceived Stress Scale
